### Interventions

*CHM intervention*: As reported previously, MZRW is composed of *Fructus Cannabis* (HuoMaRen), *Radix et Rhizoma Rhei* (DaHuang), *Radix Paeoniae Alba* (BaiShao), *Semen Armeniacae Amarum* (KuXingRen), *Fructus Aurantii Immaturus* (ZhiShi) and *Cortex Magnoliae Officinalis* (HouPo) [10]. The composition and action of each herb are summarized in Table 1[17]. The placebo was made from dextrin (76.03%), tea essence (23.61%), gardeniaflavin (0.02%) and *caramel (0.34%) to achieve color, smell, taste and texture comparable to MZRW granules. Patients were instructed to dissolve a sachet of granules (7.5 g) in 150 ml of hot water; and to* take the solution orally twice daily for 8 weeks. Quality control of the crude herbs authentication report is listed in Additional file 1.

**Table 1 T1:** Composition and action of Ma Zi Ren Wan (MZRW)

**Ingredients**	**%**	**g/****sachet**	**g/****day**	**Action**
*Fructus Cannabis*	35.7	10.8^a^	21.7	TCM: Moistening the bowel and relieving constipation
				Pharmaceutical study: 1. Purgative effect, 2. Hypotensive effect
*Radix et Rhizoma Rhei*	17.9	5.4	10.9	TCM: Draining heat and relieving constipation
				Pharmaceutical study: 1. Purgative effect, 2. Antimicrobial effect, 3. Antineoplastic and ant mutagenic effect, 4. Hemostatic effect, 5. Immunosuppressive effect, 6. Choleretic effect
*Semen Armeniacae Amarum*	17.9	5.4	10.9	TCM: Reliving constipation by guiding Qi downward
				Pharmaceutical study: 1. Laxative effect, 2. Antitussive and antiasthmatic effect, 3. Analgesic effect, 4. Antineoplastic and antimutagenic effect
*Radix Paeoniae Albo*	8.9	2.7	5.4	TCM: Nourishing Yin and retaining homeostasis
				Pharmaceutical study: 1. Analgesic effect, 2. Antimicrobial and anti-inflammatory effect, 3. Immunologic effect
*Cortex Magnoliae Officinalis*	10.7	3.3	6.5	TCM: Promoting circulation of Qi and relieving flatulence
				Pharmaceutical study: 1. Central muscle-relaxation effect, 2. Anti-emetic effect, 3. Anti-ulcerative effect 4. Central inhibitory effect, 5. Antimicrobial effect
*Fructus Aurantll Immaturus*	8.9	2.7	5.4	TCM: Promoting circulation of Qi and relieving flatulence
				Pharmaceutical study: 1. Diuretic effect, 2. Two-way effect on gastrointestinal smooth muscle, 3. Cardiovascular stimulating effect

*TCM*, traditional Chinese medicine.

^a^Each gram of *MZRW* granule is equivalent to 4.05 g of raw herbs.

*WM intervention*: An over-the-counter drug, Senokot, was selected as the active control. Each tablet comprised 7.5 mg of Sennodide B [21]. Tablets were manufactured by Reckitt Benckiser Company as circular, biconvex, greenish brown tablets. The placebo was made of starch and color to achieve an appearance comparable to Senokot. Patients were instructed to take 2 tablets at bedtime for 8 weeks. The Senokot placebo tablet was made by Guangzhou Hua hai Pharmaceuticals Co., Ltd,China according to the standards of Good Manufactory Practice (GMP).

*Rescue medication*/*enema*: Dulcolax tablets and Dulcolax suppositories [22] were provided to ensure bowel movements only in those patients without bowel movements for at least three consecutive days during the study. The rescue medication was manufactured by Boehringer Ingelheim Pharmaceuticals, Inc.,U.S.A.

MZRW granules and placebos were prepared by PuraPharm (Nanning) Pharmaceuticals Col, Ltd.,China. (lot nos. A1201839 for MZRW, and A1202071 for placebos, respectively). The entire manufacturing process, from authenticating the raw materials to the final product, was in strict compliance with the standards of Good Manufactory Practice (GMP) and Chinese Pharmacopoeia 2010 [23]. Acute toxicity testing of MZRW granules was performed on mice, in order to monitor for toxicity of the formula. The results showed that the maximum tolerance dosage was 75 g/kg, equal to 300 times the dose tested (Table 2). Chemical composition of the final products were analyzed for contamination with heavy metals, toxic elements, microbes and pesticide residue. Both MZRW and CHM placebo granules were packed in sealed opaque aluminium sachets and put in zip lock bags (28 sachets each) while Senokot and WM placebo were put in plastic bottles (56 tablets each). Only the treatment code was printed outside the package to ensure successful blinding of patients.

**Table 2 T2:** **Acute**-**toxicity of Ma Zi Ren Wan (MZRW)**

			**Dosage g/****kg**		
	**75**	**37.5**	**19.25**	**9.625**	**4.8125**
Before administered drug	22.2 ± 1.1	20.4 ± 0.6	21.1 ± 1.6	21.8 ± 1.7	23.3 ± 1.9
After administered drug	28.7 ± 4.1	25.5 ± 3.0	25.5 ± 1.1	26.1 ± 1.1	30.3 ± 1.6

Sixty ICR mice, which were divided into five groups, were used in the acute-toxic test. The mice weighed 18 to 22 g. The drug was dissolved with distilled water and administered 20 ml/kg orally. The details about dosage were as follows: 75 g/kg, 37.5 g/kg, 19.25 g/kg, 9.625 g/kg, and 4.8125 g/kg. The dosages equaled 300, 150, 75, 37.5, and 19.75 times of clinical dosage. Untoward reaction did not be observed after mice were administered the drug. Administered drug 7 days later, no one died. The weight of mice was listed as Table 2.

### Outcomes

Participants recorded stool frequency, stool form (on the 7-point Bristol stool scale, ranging from 'Separate hard lumps’ to 'Watery’), and feeling of complete evacuation (yes/no). They were also required to log intake of research medication, rescue drug and/or any other medication use throughout the study in a daily diary. Principal investigators (PIs) and research assistants (RAs) interviewed patients at the end of Week 2 (baseline), Week 4 (within treatment), Week 8 (end of treatment), and Week 16 (end of follow-up), for symptoms, compliance, and occurrence of adverse events. Data on global symptom improvement, individual bowel symptoms and stool consistency were collected.

Individual assessment of constipation and related symptoms (severity of constipation, sensation of straining, incomplete evacuation, bloating, abdominal pain/cramping, nausea and passing of gas) were recorded using a 7-point ordinal scale (0 = not at all, 6 = very severe) [see Additional file 2: Table S1] on a designated form that participants filled out during every visit [3]. Global symptom improvement was defined as the participant's subjective feeling of adequate relief of symptoms. For this purpose, participants were asked to rate their impression of changes in constipation by scoring (in comparison with their baseline (Week 2) scores) their impression of these changes from 0 to 6 to represent that they were feeling markedly worse or better at the respective extremes [3]. The response categories are collapsed to simply 'Improved’ for score 4 to 6, 'Same’ for score 3 or 'Worse’ for score 0 to 2 [24].

The primary outcome will be the response rate for CSBM during the treatment period: a clinically meaningful endpoint that combines an objective measure (number of bowel movement) with a subjective measure (feelings of patients as to completeness of defecation) [25,26]. Participants with a mean increase of CSBM ≧1/week compared with the last 14 days of the run-in period are defined as responders.

Secondary outcomes will include the response rate for CSBM during the follow-up period, including stool frequency, changes from baseline in scores of individual symptom assessment (severity of constipation, sensation of straining, incomplete evacuation, bloating, cramping/abdominal pain, nausea and passing of gas), and global symptom assessment (improved, same or worse). Safety profiles of MZRW will be assessed by determining important adverse events reported in participants’ diaries, in follow-up interviews and in clinical laboratory evaluations (for example, liver and renal function testing). During the last visit, the success of blinding would be evaluated for both investigators and patients, as to whether CHM, WM or placebo had been taken. In particular, patients are asked to rate the appearance, color, texture, taste and efficacy of the medication to try to determine whether these factors were important in their conclusion.

In addition, an objective estimate of changes in colonic transit time is made based on a commercially available radio-opaque Sitzmarks capsule (Konsyl Pharmaceuticals, INC.,Easton, MD 21601,U.S.A).

Each gelatin capsule contains 24 barium sulfate embedded polyvinyl chloride markers measuring 1 mm × 4.5 mm. Plain radiographs of the abdomen are obtained after patients swallow a capsule, for five days (120 hours) before and 8 weeks after the treatment period. Normal colonic transit is defined as expulsion of at least 80% (19 or more) markers [27,28]. For patients with six or more makers scattered throughout the colon, hypomotility or colonic inertia is suggested. If six or more markers are gathered in the rectosigmoid region with a near normal transit of markers through the rest of the colon, functional obstructive or dys-synergic defecation is suspected [4,29].

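### Global improvement is defined as adequate relief but scored as any step above no change, and the three-category outcome drops the degree of improvement that the 0-6 item collects

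*Protocol article*

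**What the plan says.** All the relevant text is in the Outcomes section of the protocol article.

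- Construct: global improvement is the participant's "subjective feeling of adequate relief of symptoms".
- Item used for that purpose: "participants were asked to rate their impression of changes in constipation by scoring", relative to Week 2, with "their impression of these changes from 0 to 6 to represent that they were feeling markedly worse or better at the respective extremes".
- Collapse: "The response categories are collapsed to simply" three groups. Improved is given "for score 4 to 6", Same is score 3, and Worse is 0 to 2. A literature source is cited for this.
- Status: the secondary outcomes list it as "global symptom assessment (improved, same or worse").

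The individual symptoms in the same section are also rated on seven levels, but they enter the secondary outcomes as changes in score. The Statistical analysis section names no test specifically for the global item.

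**The concern.** Two things do not fit together.

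First, the construct and the scoring differ. Adequate relief is a judgement that the remaining symptoms are acceptable. A change rating asks only whether the patient is better or worse than before. With 3 as Same, the first step above no change already counts as Improved. A reader who takes the definition at its word would read the proportion Improved as the proportion with adequate relief, and nothing in the item supports that.

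Second, the listed outcome discards the degree of improvement. If one arm's improved patients mostly score 6 and another's mostly score 4, with equal proportions at 3 and below, the three-category table shows no difference. This could matter for Ma Zi Ren Wan (MZRW) against senna, the comparison that the Discussion presents as new, because two active treatments may differ in how much patients improve as well as in whether they improve.

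**Working it through.** **Construct against scoring.** The plan states no expected rate, power or sample size for this outcome, so there is no figure to reproduce. Setting the statements side by side:

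| Element | What the text gives |
|---|---|
| Defined construct | adequate relief of symptoms |
| Question asked | change in constipation since Week 2 |
| Described anchors | the two extremes only |
| No change | score 3 |
| Counted as Improved | scores 4, 5 and 6 |
| Score tied to adequate relief | none |

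Score 4 is the smallest improvement because of its place in the order. The article prints no label for it.

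**Information kept after the collapse.** Under proportional odds, the information in an ordinal outcome is proportional to 1 − Σp³, where the p are the category proportions pooled over arms. Efficiency is this factor for three categories divided by the factor for seven. Its inverse is the multiple of patients needed for equal power. All score distributions below are assumptions.

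Worked example, scores 0 to 6 at 2/3/5/30/25/20/15%:

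- Seven levels: 1 − (0.02³ + 0.03³ + 0.05³ + 0.30³ + 0.25³ + 0.20³ + 0.15³) = 1 − 0.054 = 0.946.
- Three levels, at 10/30/60%: 1 − (0.10³ + 0.30³ + 0.60³) = 1 − 0.244 = 0.756.
- Efficiency: 0.756/0.946 = 0.80. Patients needed: 1/0.80 = 1.25 times.

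| Assumed % at scores 0 to 6 | Improved (4-6) | Scores 5-6 | Share of Improved at exactly 4 | Seven levels | Three levels | Efficiency | Patients needed |
|---|---|---|---|---|---|---|---|
| 2/4/9/60/15/7/3 | 25% | 10% | 60% | 0.779 | 0.765 | 0.98 | 1.02× |
| 3/5/7/45/22/12/6 | 40% | 18% | 55% | 0.896 | 0.842 | 0.94 | 1.06× |
| 3/7/10/35/22/15/8 | 45% | 23% | 49% | 0.941 | 0.858 | 0.91 | 1.10× |
| 2/3/10/30/40/10/5 | 55% | 15% | 73% | 0.907 | 0.803 | 0.89 | 1.13× |
| uniform (1/7 each) | 43% | 29% | 33% | 0.980 | 0.840 | 0.86 | 1.17× |
| 2/3/5/30/25/20/15 | 60% | 35% | 42% | 0.946 | 0.756 | 0.80 | 1.25× |
| 2/3/5/20/25/25/20 | 70% | 45% | 36% | 0.953 | 0.648 | 0.68 | 1.47× |
| 1/2/3/19/25/28/22 | 75% | 50% | 33% | 0.945 | 0.571 | 0.60 | 1.65× |

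The loss runs from about 2% to 40%. Patients at exactly 4 make up a third to nearly three quarters of those counted as Improved, so the meaning of that score decides how the Improved rate should be read.

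These figures describe a treatment effect that shifts the whole scale. An effect confined to scores 4 to 6, as in the example of 4 against 6 above, is a different case: the three categories would miss it completely.

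**The case against.** The case for leaving the text alone has real parts.

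- *The label is accurate.* On a scale where 3 is Same, calling 4 to 6 Improved is correct, and nowhere does the article plan to report an adequate-relief rate. This stands: the fault lies in the definition, and harm follows only if Improved is read through it.
- *No bias between arms.* A reader might infer that the lenient cut favours one treatment. The documents do not support that, because the same cut applies in all three blinded arms.
- *The collapse is prespecified and sourced.* That answers any worry about a cut chosen after seeing data. The source cannot be checked here, and the article does not say that it equates scores 4 to 6 with adequate relief.
- *The raw scores survive.* All seven levels are collected, and an analysis plan that is not shown could use them. The outcome as published would still be the three-category one and would still carry the wrong construct.
- *Graded information exists elsewhere.* Constipation severity and six other symptoms keep their 0-6 scores. Stool frequency and colonic transit are also measured, and the primary outcome, response in complete spontaneous bowel movements, is untouched. A reader might infer that the collapse removes most of the trial's ability to separate MZRW from senna. That does not follow: these outcomes also inform the comparison, and even the worst case above keeps 60% of the information in this one item.
- *The distributions are invented.* They are. The planning rates of 40%, 20% and 10% in the Sample size calculation section concern a different outcome and do not show that most patients will score above 3.

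**Conclusion.** The mismatch between construct and scoring is certain from the text and needs correcting: Improved means any patient-rated improvement since baseline, and its rate cannot be presented as adequate relief. It does not follow that the trial will overstate relief, because the planned label is Improved, or that patients scoring 4 lack adequate relief, because the wording of that score is not shown.

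The loss from three categories is certain in direction and uncertain in size: about 2% to 40% of the information in this item, given proportional odds and the assumed distributions. It is small if most patients answer Same and larger if answers spread over 4 to 6. It is a cost in efficiency on one secondary outcome. The correction is worth making because it is nearly free.

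**What to change.** 1. In the Outcomes section, describe the outcome as patient-rated change in constipation since baseline (Week 2), and delete the reference to adequate relief.
2. State that the full 0-6 score is compared between arms with an ordinal method, either a proportional-odds model or a Wilcoxon test.
3. Keep improved, same or worse as a descriptive table by arm.

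Cost: a change of wording and a slightly less simple headline summary for one secondary outcome. No new data are needed, since the seven levels are already recorded. According to the Trial status section, 20 participants had been enrolled at submission and none had completed treatment. The Assignment and blinding section keeps statisticians blinded until the study ends. At that stage the change could be made without knowledge of results.

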### Recruitment procedures

Three strategies are used to recruit participants with FC. The first relies on the participant bank of over 600 patients, built up from prior research team work in functional constipation related studies since 2007. The second relies on referrals from the two study sites (Lee Kee Memorial Dispensary and Li Ka Shing Specialist Clinic of Prince of Wales Hospital) from our co-investigators (Co-Is). The third strategy consists of posted advertisement in local newspapers and a press conference to introduce our research.

All patients diagnosed with functional constipation by the physicians (Co-Is) are referred to the principal investigator (PI) and/or to the research assistants (RA) to determine whether they meet diagnostic criteria of excessive constipation according to TCM theory. There is inconsistency among different TCM practitioners regarding pattern differentiation for FC. If any inconsistency occurs for an individual patient concerning pattern identification, the other senior CMP with more than 20 years clinical practice will be invited to make the diagnosis of TCM pattern independently to ensure the consistence of the diagnosis. The aims, procedures and nature of the study, and possible side effects are explained by the PI and/or the RAs before a written consent form is obtained from each subject who agrees to participate. Moreover, patients are informed that they are free to withdraw at any time during the study. All patients undergo a 2-week, drug-free observation period. Meanwhile, they have to complete a stool and symptom diary to confirm their diagnosis. Blood tests of liver and renal function (blood urea, creatinine, alanine transaminase and aspartate transaminase, alkaline phosphatase and bilirubin), and plain abdominal X-ray for colonic transit study are arranged. Patients are considered eligible for the study if their diaries reflect conformance with the Rome III criteria for a diagnosis of functional constipation, and if they also have normal liver and renal function. Recruited patients will obtain their intervention assignment from the PI and/or RAs.

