### Assignment and blinding

Block randomization was carried out in 1:1:1 ratio according to the sequence generated with Random Allocation Software (Version 1.0.0), Isfahan, Iran. The RA assigns treatments according to the codes that are kept in opaque sealed envelopes with consecutive randomization numbers. Treatment assignments will not be revealed and are blinded to the patients and investigators (including statisticians) until the entire study is completed. At the last visit, all patients and the PI/RAs will complete a questionnaire about which treatment (CHM group, WM group or placebo group) the patients received to evaluate the success of blinding. Code breaks should only occur in exceptional circumstances when knowledge of the actual treatment is absolutely essential for further management of the patient.

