### Sample size calculation

From the results of the placebo-control study, the response rate of MZRW was 43.3% [14]. Assuming the response rates for TCM, senna and placebo were 40%, 20% and 10%, respectively. Therefore, 82 patients per treatment group were deemed sufficient to achieve 80% power in detecting treatment differences, based on two-sided Chi-square test without continuity correction at a significance level of 0.025 (used to maintain the overall significance level at 5%). Further, assuming a 15% dropout rate, we concluded that a total of 291 patients (97 per arm) would need to be recruited to ensure statistically significant results. The calculation is performed using StudySize 2.0 software, London, UK.

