### Statistical analysis

All efficacy and safety analyses will be conducted according to the intention-to-treat (ITT) principle. Missing values will be imputed by the last-observation-carried-forward method. The statistical analysis will be performed using the Statistical Packages of Social Sciences (SPSS) for Windows version 16.0. The statistical significance is defined as two-sided *P* value of <0.05. Baseline characteristics will be reported as mean (SD). Baseline differences among the groups will be assessed with the use of Student’s t-test for normally distributed continuous variables and the non-parametric Mann-Whitney U test for non-normally distributed variables. For categorical variables, chi-squared test or Fisher’s exact test will be used. Comparisons between groups will be conducted by using an analysis of covariance (ANCOVA) with baseline as covariate. All items and subscales will be compared between groups for each 6-week treatment using ANCOVA, with treatment group as a factor in the model and baseline as the covariate. The changes from baseline to endpoint of treatment in scores will be tested with repeated measure analysis of variance (ANOVA). Within group differences will be assessed with paired t-test for normally distributed data and Wilcoxon signed-rank test for non-normally distributed data.

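### The run-in transit film and the clinic are known before assignment but are not named as covariates for the primary responder comparison; prespecifying them is cheap and may add a little power

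*Protocol article*

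**What the plan says.** All in the protocol article.

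- **Recruitment procedures.** In the two-week drug-free run-in, before assignment, blood tests and "plain abdominal X-ray for colonic transit study are arranged". The section on data collection counts two sets of films per patient.
- **Outcomes.** Normal transit means that 19 or more of 24 markers have been expelled. Otherwise the pattern of retained markers is read: "For patients with six or more makers scattered throughout the colon, hypomotility or colonic inertia is suggested", while markers gathered in the rectosigmoid region raise suspicion of an outlet-type disorder. The film serves only the transit outcome.
- **Study design.** Patients come from a general outpatient clinic, a hospital specialist clinic and university Chinese medicine clinics.
- **Assignment and blinding.** Allocation is 1:1:1 in blocks; no stratification factor is stated.
- **Sample size calculation.** The assumed rates are "Assuming the response rates for TCM, senna and placebo were 40%, 20% and 10%, respectively", and the size is "based on two-sided Chi-square test without continuity correction at a significance level of 0.025".
- **Statistical analysis.** "Comparisons between groups will be conducted by using an analysis of covariance (ANCOVA) with baseline as covariate". Neither transit nor clinic is named, and no test is expressly assigned to the between-arm comparison of the binary primary endpoint.

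**The concern.** Two baseline facts that could bear on response will be on file for each patient before assignment, at no extra cost. If either predicts response, an unadjusted comparison leaves explainable variation between patients as noise. MZRW versus senna has the least room for that. At 82 per arm and two-sided 0.025, its power is about 71.5%, against 99.0% for MZRW versus placebo. The one covariate the article names sits in an ANCOVA, which suits symptom scores but not a yes/no responder. The article therefore gives the primary comparison no workable adjusted model.

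**Working it through.** **Inputs from the article:** 40% (MZRW) and 20% (senna); 82 per arm, 97 after dropout; two-sided 0.025. **Assumptions, because the article gives no figures:** the transit mix (normal/slow/outlet 50/30/20%) and the strength of association with response.

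**1. The plan's own figure.** The pooled-variance formula without continuity correction is

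n = [z(α/2)·√(2p̄q̄) + z(β)·√(p₁q₁ + p₂q₂)]² / (p₁ − p₂)²,

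with p̄ = 0.30, 2p̄q̄ = 0.42 and p₁q₁ + p₂q₂ = 0.24 + 0.16 = 0.40.

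- Two-sided 0.05: (1.960×0.6481 + 0.8416×0.6325)² / 0.04 = 81.2, so 82. This is the stated number.
- Two-sided 0.025: (2.2414×0.6481 + 0.8416×0.6325)² / 0.04 = 98.5, so 99.
- Power of 82 per arm at 0.025: z = (0.2×√82 − 1.4526) / 0.6325 = 0.567, or 71.5%. For 97 per arm it is 79.3%.

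The unadjusted starting point is therefore 71.5%, not 80%.

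**2. Gain from adjusting for transit.** Keep the overall rates at 40% and 20%, and let normal transit have a given odds ratio (OR) of response against the other two classes. With class shares w, class rates p₁ and p₂, and class differences d = p₁ − p₂, the variance of the standardised risk difference relative to the unadjusted one is

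R = {Σ w(p₁q₁ + p₂q₂) + ½ Σ w(d − 0.20)²} / 0.40,

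and the trial behaves as if it had n/R per arm.

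Example, OR 3. The class rates are 0.528 and 0.272 on MZRW, and 0.283 and 0.117 on senna. The first sum is 0.5×0.452 + 0.5×0.301 = 0.377 and the second term is ½×0.045² = 0.001. R = 0.378/0.40 = 0.944; 82/0.944 = 86.9; power 74.2%.

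| Assumed OR | Power, 82 per arm, 0.025 | Equivalent patients saved per arm |
|---|---|---|
| 1 | 71.5% | 0 |
| 1.5 | 71.9% | 0.7 |
| 2 | 72.6% | 1.9 |
| 3 | 74.2% | 4.6 |
| 5 | 77.0% | 9.1 |

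With clinic effects added (two clinics at the square root of the OR above and below the third), power is 72.1% at OR 1.5, 73.3% at OR 2 and 75.8% at OR 3.

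**3. Simulation of the logistic model.**

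- Transit alone, ORs 1/0.5/0.25: from 72% to 74% (82 per arm) and from 79% to 82% (97).
- Transit alone, ORs 1/0.33/0.1: from 71% to 76% and from 80% to 85%.
- Transit plus clinic with a standardised risk difference: about +3 points under moderate effects and +6 to 7 under strong ones.
- Both factors irrelevant: the adjusted and unadjusted powers agree within half a point (71.3% and 70.9% at 82 per arm; 80.7% and 81.0% at 97).
- Type I error of the adjusted test: up to about 3%, against 2.5 to 2.7% for the chi-square.

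The form of adjustment matters. A Cochran-Mantel-Haenszel test loses about 1 point when transit is irrelevant (72.1% to 71.1%). With nine transit-by-clinic strata, transit irrelevant and a clinic OR of 1.5, it loses about 1.5 points (72.3% to 70.8%). Main-effect covariates avoid most of that.

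**4. Does adjustment rescue the sample size?** To reach 80% with 82 per arm, R would have to fall to 82/98.5 = 0.83. At OR 5 it is 0.889. It does not.

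**The case against.** The strongest case against is that the article contains no error here. Covariates are commonly left to an analysis plan, which is not shown. The chi-square is stated for sizing, and sizing on an unadjusted test is compatible with an adjusted analysis. **This stands:** a reader might infer that the primary test is fixed as unadjusted, but the article says only how the trial was sized and which covariate it names.

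A reader might also infer that power on MZRW versus senna is being thrown away. The documents do not support that. No section links transit pattern or clinic to response, and the film readings are worded as suggestions and suspicions. The case for clinic is weaker still: recruitment also runs through a patient bank and advertisements, and all patients meet the same entry criteria. **This stands too**, and it limits the claim to a possible gain.

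Nor is chance imbalance a bias. With half the patients in normal transit and 97 per arm, the standard deviation of the between-arm difference in that share is √(2×0.25/97) = 7.2 points. A gap of 10 points or more (at least 10 patients) then arises in about 17% of randomisations. The error rate of the chi-square already allows for this; adjustment buys precision, not validity.

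What the objection does not remove is that the values are already collected, the named ANCOVA does not fit a binary endpoint, and the covariates can be chosen credibly only before unblinding.

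**Conclusion.** The point holds as a modest, low-cost improvement, not as a flaw that invalidates the comparison. Under the assumed transit mix and moderate effects, MZRW versus senna gains about 0 to 3 points of power. A gain of 5 to 7 points needs strongly prognostic factors, and if they are not prognostic there is essentially no loss. All of these figures rest on assumed associations.

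It would be wrong to read adjustment as a cure for the trial's power. Even at OR 5 for transit, 82 per arm reaches 77.0% at two-sided 0.025. The mismatch between 82 and 99 per arm is larger and separate. So is the conflict between the 0.025 used for sizing and the analysis section's rule, "The statistical significance is defined as two-sided *P* value of <0.05". Both should be settled first.

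**What to change.** Before unblinding, add to the analysis plan, or confirm if it is already there:

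- Primary analysis: logistic regression of responder status on arm, with run-in retained-marker count and clinic as main effects. Transit category with a missing/unclassified level is the alternative. The count is safer, since six or more retained markers may fit neither abnormal pattern clearly.
- Report the standardised risk difference with its interval, and keep the unadjusted chi-square as supportive.
- Use run-in values only, so that nothing measured after assignment enters the model.
- State a rule for unreadable or missing films.

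**Cost:** a sentence or two and slightly more analysis work, with no new patients, visits or data. **Downside:** the adjusted test may be marginally liberal at this size (about 3% against a nominal 2.5% in simulation). The sample-size statement needs its own correction.
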